## Abstract

**Background**: Janus kinase (JAK) inhibitors have emerged as a new class of disease-modifying anti-rheumatic drugs in the treatment of rheumatoid arthritis (RA). However, herpes zoster is one of the common adverse events of JAK inhibitors, including upadacitinib, which is especially high in Japanese patients with RA compared to those from Western countries. Recombinant zoster vaccine (Shingrix^®^) is an adjuvanted subunit vaccine containing varicella-zoster virus (VZV) glycoprotein E (gE) that is effective in adults over 50 years of age. Despite this, no studies have examined its immunogenicity in Japanese patients receiving upadacitinib. Therefore, this study aims to examine the effectiveness of the recombinant zoster vaccine in Japanese patients with RA receiving upadacitinib. **Methods**: This is a single-center, exploratory, interventional, open-label, parallel triple-arm, prospective study. A total of 69 patients (23 in each group) aged 50 years or over and treated with a stable dose of methotrexate (MTX) monotherapy (6–12 mg/week), upadacitinib monotherapy (15 mg/day), or MTX (6–12 mg/week) + upadacitinib 15 mg/day (combination) for at least 1 month prior to study entry will be included. Moreover, all three groups will receive two intramuscular injections of the recombinant zoster vaccine at 8-week intervals. The primary endpoint is the proportion of positive anti-gE antibodies 4 weeks after the second injection. Secondary endpoints include RA disease activity, positive gE-specific CD4+ T-cells, and VZV-specific antibodies at indicated time points. Data on outcome measures will be collected at baseline and at 4, 8, 12, and 20 weeks. Endpoints will be summarized using descriptive statistics from baseline therapy, and results will be compared in an exploratory manner. **Discussion**: Despite the limited generalizability due to its design as a single-center, single-ethnic study, small sample size, and short observation period, this study provides evidence on the effectiveness and tolerability of recombinant zoster vaccine in Japanese patients with RA receiving upadacitinib.

## 1. Introduction

Rheumatoid arthritis (RA) is a chronic inflammatory disease causing progressive joint destruction and physical impairment if untreated [1]. Significant progress has been made in the treatment of RA over the decades. Conventional synthetic disease-modifying anti-rheumatic drugs (csDMARDs), such as methotrexate (MTX), and biological DMARDs, including tumor necrosis factor (TNF) inhibitors, interleukin (IL)-6 receptor antibodies, and abatacept, have become widely used for RA. Targeted synthetic DMARDs (tsDMARDs), also known as Janus kinase (JAK) inhibitors, have emerged as a new class of DMARDs. Currently, five JAK inhibitors (tofacitinib, baricitinib, upadacitinib, peficitinib, and filgotinib) are available in Japan, offering equivalent or superior effectiveness compared to existing bDMARDs [2]. This has made remission or low disease activity achievable goals in most patients. However, challenges remain for those who are refractory to any treatment, referred to as difficult-to-treat RA [3,4].

Herpes zoster is a common adverse event associated with JAK inhibitors, occurring in approximately 3–5% of patients with RA [5]. Particularly, Japanese patients with RA exhibit a higher incidence of herpes zoster compared to their European and American counterparts [5]. While recombinant zoster vaccine (Shingrix^®^), a subunit vaccine containing varicella-zoster virus (VZV) glycoprotein E (gE) with the AS01B adjuvant system, has been reported to be effective in adults over 50 years of age [6], JAK inhibitors (tofacitinib and baricitinib) partially attenuate its immunogenicity at 1.5 months post-administration [7]. This was consistent with a case report of a tofacitinib-treated patient who developed herpes zoster despite vaccination [8]. Furthermore, the vaccine is known to cause RA flares within 12 weeks after administration in some cases [8,9,10]. Nevertheless, studies investigating the immunogenicity of this vaccine in the presence of upadacitinib are limited, particularly among Japanese patients.

To address this gap, we aim to examine the immune response to the recombinant zoster vaccine Shingrix^®^ in Japanese patients with RA receiving upadacitinib. We assess immunogenicity at week 4 and RA flare ups to week 12 after the second Shingrix^®^ dose in patients receiving MTX (6–12 mg/week) monotherapy (Arm 1), upadacitinib (15 mg/day) monotherapy (Arm 2), and MTX (6–12 mg/week) + upadacitinib (15 mg/day) combination therapy (Arm 3). Immunogenicity and RA flares will be determined as previously described (immunogenicity [11] and RA flare [7,10]). In addition to humoral immune response (anti-gE-specific antibodies and anti-VZV-specific antibodies), cellular immune response (e.g., VZV-specific T-cell response) will be tested in this study, since the latter is a better surrogate marker for protection against herpes zoster [12,13,14]. Both humoral and cellular immunity have been reported to peak approximately 1 month after the second shot of the vaccine [15]; thus, the time point for the primary endpoint was set at 4 weeks after the second shot. In addition, the time points for secondary endpoints were set at 4 weeks after the first and second shots. Moreover, since recombinant zoster vaccine is associated with potential exacerbations or new onset of immune-mediated disease [16], not only disease activity of RA but also other adverse events will be carefully monitored.

The objective of this study is to investigate the immunogenicity and disease flares following recombinant zoster vaccination (Shingrix^®^) in Japanese patients with RA receiving MTX (6–12 mg/week) + upadacitinib (15 mg/day) combination therapy.

This is an exploratory, interventional, open-label, parallel triple-arm, prospective study. The three arms comprise the following regimens administered at patient registration:(1)MTX monotherapy (6–12 mg/week).(2)Upadacitinib monotherapy (15 mg/day).(3)MTX (6–12 mg/week) + upadacitinib (15 mg/day) (primary evaluation target) combination therapy.

All patients in the three groups will receive two intramuscular injections of the recombinant zoster vaccine at 8-week intervals. It should be noted that MTX can be used up to 16 mg/week in Japan. However, the dose indicated in the study was based on the typical dose administered in most institutions (6–12 mg/week) [17,18]. The upadacitinib dose (15 mg/day) was set as the approved dose.

## 2. Methods

### 2.1. Study Setting

This is a single-center trial conducted at Osaka Metropolitan University Hospital, Osaka, Japan.

### 2.2. Trial Registration

This study was registered with the Japan Registry of Clinical Trials (jRCTs051220105) before enrolling the first participants (14 October 2022).

### 2.3. Eligibility Criteria

The eligibility criteria include the following: (1) fulfilled the 1987 or 2010 classification criteria for RA [19,20]; (2) aged over 50 years; (3) provided written informed consent; (4) received MTX monotherapy (6–12 mg/week), upadacitinib monotherapy (15 mg/day), or MTX (6–12 mg/week) + upadacitinib (15 mg/day) combination therapy for at least 1 month prior to the study entry; (5) and able to adhere to follow-ups based on the research schedule. Patients with prior exposure to JAK inhibitors other than upadacitinib may be enrolled (up to 20% of the total study population) if they responded to previous JAK inhibitors but had to discontinue treatment due to adverse events (1-week wash out period is required prior to the first dose of the study drug).

The exclusion criteria include the following: (1) required hemodialysis; (2) pregnant or lactating; (3) had severe liver dysfunction (Child–Pugh C); (4) had serious infection or active tuberculosis; (5) presented with neutropenia (<1000/mm^3^), lymphopenia (<500/mm^3^), or anemia (haemoglobin <8 g/dL); (6) previously received recombinant zoster vaccine (Shingrix^®^); (7) previously received a live herpes zoster vaccine within 8 weeks before enrollment; (8) developed herpes zoster or had related symptoms within 6 months before enrollment; (9) received any vaccine within 4 weeks before enrollment or planned to receive other vaccines (except Shingrix^®^) between enrollment and 4 weeks after the second shot of Shingrix^®^; (10) congenital or acquired immunodeficiency; (11) received prednisolone (equivalent) >10 mg; (12) discontinued prior JAK therapy due to insufficient efficacy; and (13) otherwise deemed unsuitable for participation in this study.

### 2.4. Who Will Take Informed Consent?

The principal investigator or co-investigator will obtain written informed consent.

### 2.5. Additional Consent Provisions for Collection and Use of Participant Data and Biological Specimens

An additional 6 mL of peripheral blood will be drawn from the enrolled patients. Serum, peripheral blood mononuclear cells (PBMCs), and RNA extracted from PBMCs will be stored for ancillary research.

## 3. Interventions

### 3.1. Explanation for the Choice of Comparators

The study will employ two comparator groups to assess the effect of the recombinant zoster vaccine (Shingrix^®^): MTX monotherapy (6–12 mg/week) and upadacitinib monotherapy (15 mg/day).

### 3.2. Intervention Description

All patients across the three arms will receive two intramuscular injections of the recombinant zoster vaccine (Shingrix^®^) at 8-week intervals (Figure 1).

### 3.3. Criteria for Discontinuing or Modifying Allocated Interventions

#### 3.3.1. Criteria for Discontinuing Allocated Interventions

Allocated interventions are discontinued for the following situations:(1)When the patient withdraws the informed consent.(2)When a principal investigator or co-investigator judges that it is difficult to continue the research due to worsening of the primary disease, complications, or the occurrence of serious adverse events.(3)When there is a need to administer contraindicated drugs.(4)When serious deviations from the research protocol occur, such as violations of the Clinical Research Act and its implementation regulations, inclusion, or exclusion criteria. Examples of serious deviations are listed below, but are not limited to these events:
Medication non-compliance: interruption of oral medication for 14 consecutive days.Patients who did not receive at least one dose of Shingrix^®^ as scheduled.Patients who received other vaccines between obtaining informed consent and 4 weeks after the second Shingrix^®^ dose.(5)When pregnancy of the study subject is discovered.(6)When the study is discontinued.(7)When the drugs being administered (MTX and Upadacitinib) are discontinued or are found to have been discontinued prior to intervention.(8)When the principal investigator or co-investigator determines that it is difficult to continue the study.

#### 3.3.2. Criteria for Modifying Allocated Interventions

The Shingrix^®^ dosing interval can be extended up to 10 weeks.

### 3.4. Strategies to Improve Adherence to Interventions

At each visit, the principal investigator and co-investigators monitor drug adherence, adverse events, laboratory tests, and the date of the next scheduled visit.

### 3.5. Relevant Concomitant Care Permitted or Prohibited During the Trial

Concomitant use of other anti-rheumatic drugs, analgesics, and necessary medications (except other bDMARDs and JAK inhibitors) is permitted. However, dose changes of anti-rheumatic drugs, including MTX, upadacitinib, and glucocorticoids, are prohibited from the time of consent acquisition until 4 weeks after the second Shingrix^®^ dose.

### 3.6. Provisions for Post-Trial Care

Compensation for those who suffer harm from study participation will be provided up to 12 months post-disease/injury, based on consultation with the principal investigator, medical insurance company, and other relevant departments. The amount of compensation will be determined based on the severity of the adverse events.

Further ancillary research will be conducted after the research plan has been approved by the Ethics Committee, and patient consent will be obtained prior to its implementation.

## 4. Outcomes

### 4.1. Primary Endpoint

Proportion of participants with positive anti-gE antibodies at 4 weeks after the second Shingrix^®^ dose.

### 4.2. Secondary Endpoints

(1)Presence or absence of RA flares from enrollment to 12 weeks after the second Shingrix^®^ dose.(2)Proportion of participants with positive anti-gE antibodies at 4 weeks after the first Shingrix^®^ dose.(3)Antibody titre of anti-gE antibodies at 4 weeks after the first and second Shingrix^®^ doses.(4)Proportion of gE-specific CD4+ T-cells at 4 weeks after the first and second Shingrix^®^ doses.(5)Antibody titre of VZV-specific antibodies at 4 weeks after the first and second Shingrix^®^ doses.(6)Changes in RA disease activity.

### 4.3. Evaluation of Primary and Secondary Endpoints

#### 4.3.1. Positive Anti-gE Antibodies

This is defined as having an antibody titre 4 weeks after the first or second Shingrix^®^ doses that is increased 4 or more times from baseline (before Shingrix^®^ injection at week 0) or the cutoff value calculated, as in previous reports [11]. The time points for this assessment were determined based on a previous study [11]. Anti-gE antibodies will be evaluated using an enzyme-linked immunosorbent assay (ELISA) by AbbVie Deutschland GmbH and Co.

#### 4.3.2. RA Flare

This is defined based on the following: (1) judgment by the attending physician, (2) administration of new or increased dose of glucocorticoids, (3) increased or addition of anti-rheumatic drugs, and (4) increased disease activity based on a Disease Activity Score (DAS)28-C-reactive protein (CRP) ≥0.6. The observation period was set until 12 weeks after the second Shingrix^®^ dose based on previous studies [7,10]. However, an extension of 2 weeks (20 -2 to +4 weeks from the enrollment of the study) is allowed.

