#### 4.3.5. Changes in RA Disease Activity

RA disease activity will be monitored using the DAS28-CRP, DAS28-erythrocyte sedimentation rate (DAS28-ESR), simplified disease activity index (SDAI), and clinical activity index (CDAI).

If flare is observed, treatment will be at the discretion of each attending physician and will not be limited by this study (Table 1).

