## 5. Assignment of Interventions: Allocation

### 5.1. Sequence Generation

Not applicable to this study.

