### 5.4. Who Will Be Blinded

The treatment arm of each participant is not disclosed to the outcome assessors for blinded assessment of anti-gE antibodies or gE-specific CD4+ T-cells.

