### 7.3. Secondary Endpoints

(1)Presence or absence of RA flares from enrollment to 12 weeks after the second Shingrix^®^ dose.

The numbers and proportions of patients with RA flares are summarized for each group.

(2)Proportion of positive anti-gE antibodies at 4 weeks after the first Shingrix^®^ dose.

The number and proportion of patients positive for anti-gE antibodies at 4 weeks after the first Shingrix^®^ dose will be summarized for each group. Evaluations will also be conducted after adjusting for confounders.

(3)Antibody titre of anti-gE antibodies at 4 weeks after the first and second Shingrix^®^ doses.

Means, standard deviations, medians, interquartile ranges, minimum values, maximum values, 95% confidence intervals, and numbers of missing values are described for each group.

(4)Proportion of gE-specific CD4+ T-cells at 4 weeks after the first and second Shingrix^®^ doses.

Means, standard deviations, medians, interquartile ranges, minimum values, maximum values, 95% confidence intervals, and numbers of missing values are described for each group.

(5)Antibody titer of VZV-specific antibodies at 4 weeks after first and second Shingrix^®^ doses.

Means, standard deviations, medians, interquartile ranges, minimum values, maximum values, 95% confidence intervals, and numbers of missing values are described for each group.

(6)Changes in RA disease activity.

Means, standard deviations, medians, interquartile ranges, minimum values, maximum values, 95% confidence intervals, and numbers of missing values are described for each group.

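### RA flare is reported as one count per arm although three of its four criteria are decisions of an unblinded physician: report each criterion by arm and state how they combine

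*Protocol article*

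**What the plan says.** All references are to the protocol article.

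- **Endpoint.** The Introduction names immunogenicity and disease flares together as the study objective. Section 4.2 lists flare first among the secondary endpoints, as a yes/no outcome: "Presence or absence of RA flares from enrollment to 12 weeks after the second" vaccine dose.
- **Definition.** Section 4.3.2 gives four criteria. Three are "1) judgment by the attending physician, (2) administration of new or increased dose of glucocorticoids, (3) increased or addition of anti-rheumatic drugs". The other is "4) increased disease activity based on a Disease Activity Score (DAS)28-C-reactive protein (CRP) ≥0.6". The section does not say whether one criterion is enough or all are needed, or from which visit the 0.6 is measured.
- **Who decides on treatment.** Section 4.3.5 says that once a flare is seen, "treatment will be at the discretion of each attending physician" and is not limited by the study.
- **Design and blinding.** The Introduction states: "This is an exploratory, interventional, open-label, parallel triple-arm, prospective study". Arms are defined by the therapy in use at registration, and section 5.1 on sequence generation reads "Not applicable to this study". Section 5.4 withholds the arm only for "blinded assessment of anti-gE antibodies or gE-specific CD4+ T-cells".
- **Analysis.** Section 7.3(1): "The numbers and proportions of patients with RA flares are summarized for each group". No breakdown by criterion is given. Section 7.3(6) separately summarises change in disease activity by arm.
- **Dose changes.** Section 3.5 prohibits dose changes of anti-rheumatic drugs and glucocorticoids from consent until 4 weeks after the second vaccine dose. Section 7.1.2 excludes patients with such changes from the per protocol set.

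**The concern.** The three arms are to be compared, if only in an exploratory way, and section 3.1 names two of them as comparators. The threshold at which a physician calls a flare, adds a glucocorticoid or steps up an anti-rheumatic drug may differ with the background therapy. The Introduction itself suggests one route: it notes that MTX may be used above the study range in Japan, while upadacitinib is set at its approved dose. The options for increasing a drug may therefore differ between arms. That is an inference; the documents report no such difference in behaviour.

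A single count mixes these decisions with measured disease activity. If it differs between arms, the report cannot say which of the two produced the difference. What is at stake is the reading of one of the two outcomes named in the objective. No confirmatory test is involved, since none is planned for flare.

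**Working it through.** **1. The plan's own figures.** Section 4.4 gives 20 evaluable patients per group and 10% dropout: 20 / (1 − 0.10) = 22.2, rounded up to 23; 3 × 23 = 69. This reproduces. The documents give no expected flare rate, so the rates below are assumptions chosen to show a range.

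**2. Who determines each criterion.** Criterion 1 is the attending physician's judgement. Criteria 2 and 3 are treatment decisions, which section 4.3.5 leaves to the same physician. Only criterion 4 is a measurement. Section 5.4 describes no blinding for any of the four.

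**3. If any one criterion suffices.** Let p be the proportion with a measured flare (criterion 4), equal in both arms. Let j be the proportion of the remaining patients counted as flares through criteria 1 to 3 only.

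Composite = p + (1 − p) × j, so the arm difference = (1 − p) × (j_B − j_A).

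| p (both arms) | j_A v j_B | Composite A v B | Difference | Flares per 20 |
|---|---|---|---|---|
| 10% | 5% v 25% | 14.5% v 32.5% | 18 points | 2.9 v 6.5 |
| 20% | 5% v 25% | 24% v 40% | 16 points | 4.8 v 8.0 |
| 30% | 10% v 30% | 37% v 51% | 14 points | 7.4 v 10.2 |
| 30% | 5% v 15% | 33.5% v 40.5% | 7 points | 6.7 v 8.1 |

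Over all nine combinations of p = 10%, 20%, 30% with j = 5% v 15%, 5% v 25%, 10% v 30%, the difference runs from 7 to 18 points. The measured criterion alone gives 0 in every case, by construction.

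**4. If all criteria are required.** Composite = p × q, where q is the chance that a patient with a measured flare is also judged and treated as one. With p = 30% and q = 0.3 v 0.7: 0.30 × 0.3 = 9% and 0.30 × 0.7 = 21%, a difference of 12 points. Physician decisions can no longer create a flare alone, but they can still create an arm difference.

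**5. Precision.** With n = 20 per arm and a common rate r, the 95% half-width of a difference is 1.96 × √(2r(1 − r)/20). This is 18.6 points at r = 10%, 24.8 at 20% and 28.4 at 30%.

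**6. What is already planned.** Section 7.3(6) gives means, medians, spread and confidence intervals for change in disease activity, with DAS28-CRP among the indices in section 4.3.5. It does not give the proportion of patients reaching the 0.6 criterion, and it does not link measured change to the patients counted as flares. Table 1 schedules disease activity and CRP at every visit, so the data for that proportion will exist.

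**7. Dose changes, side by side.** Section 3.5 prohibits them until 4 weeks after the second dose (week 12 of 20), and section 7.1.2 removes such patients from the per protocol set. Section 4.3.2 counts new or increased drugs as flare criteria from enrolment, and section 4.3.5 leaves flare treatment unrestricted. A patient whose dose is raised for a flare before week 12 therefore meets a flare criterion in the full analysis set and leaves the per protocol set for the same event.

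**The case against.** The other side has several good points.

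- *This is detail for the analysis plan.* The article is condensed and the analysis plan is not shown; a component table may be in it, and section 7.3 does not rule one out. This limits the weight of the point. But the article does fix the endpoint and its summary, and the definition leaves open how the criteria combine.
- *Measured activity is already reported by arm.* True, and this answers part of the concern. It does not give the proportion meeting the 0.6 criterion.
- *Discretion is restricted until week 12.* Section 3.5 does say so for dose changes, but criterion 1 is unrestricted throughout, the last 8 of the 20 weeks are open, and section 4.3.5 says the opposite about flare treatment.
- *The endpoint is secondary, descriptive and non-randomised.* This stands. Confounding by the reason for each background therapy affects any flare comparison, and a breakdown does not remove it. The illustrated differences are also smaller than the half-widths in step 5.

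A reader might go further and infer that DAS28-CRP should become the main basis for comparing arms. The documents do not support that. No blinded DAS28 assessor is described, so this score too is taken at the open-label site. It misses flares between visits, and it is lowered by treatment already given, which brings physician behaviour back in.

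**Conclusion.** The point holds in a limited form. A single flare count per arm cannot separate disease activity from the decisions of a physician who knows the arm, and the planned summaries of DAS28-CRP change close this gap only in part. The size is unknown. The 7 to 18 points apply to an any-criterion rule and the 12 points to an all-criteria rule, and both rest on assumed rates.

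A reader might also infer that the flare comparison is biased, or that judgement alone can create a flare. The documents show no difference in physician behaviour between arms, and the second inference is true only if any one criterion suffices, which section 4.3.2 does not say. The finding is about what the result can be taken to mean. It is worth acting on because flare is in the objective and the data needed are already scheduled.

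**What to change.** In section 7.3(1), with matching wording in section 4.3.2:

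1. Keep the composite as the flare endpoint, and state whether any one or all of the criteria are required.
2. State the reference visit for the 0.6 rise in DAS28-CRP and the visits at which it is assessed. Table 1 records disease activity at every visit from before enrolment to week 20 but marks flare only at week 20.
3. Report each of the four criteria separately by arm, including the proportion with a DAS28-CRP rise of at least 0.6 at scheduled visits, as a supporting analysis read alongside the composite.
4. State the limits with the results: DAS28-CRP is less discretionary but is scored at the open-label site, misses flares between visits and is lowered by earlier treatment; the arms are not randomised, so confounding remains.
5. Reconcile sections 3.5 and 7.1.2 with sections 4.3.2 and 4.3.5 on dose changes before 4 weeks after the second dose, and say in which analysis set flares are counted.

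The cost is a few table rows and some wording. No extra visits, staff or patients are needed for the DAS28-CRP row; the other three rows need the criterion met to be recorded for each flare. If the analysis plan already contains the breakdown, only items 1, 2 and 5 remain for the protocol text.
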